## Abstract

**Background:**

Postoperative sleep disturbance (POSD) affects up to 62% of patients undergoing gynecologic laparoscopy and is associated with prolonged recovery, chronic pain, and cardiovascular complications. Transcutaneous auricular vagus nerve stimulation (taVNS) modulates thalamocortical oscillations through afferent vagal pathways, offering a potential non-pharmacological mechanism to prevent acute sleep disruption during critical perioperative neuroplastic windows. This study aims to evaluate whether perioperative dual-session taVNS reduces the incidence of clinically significant POSD compared with sham stimulation.

**Methods:**

This single-center, randomized, double-blind, sham-controlled trial is planned to enroll 116 patients aged 18–65 years scheduled for elective gynecologic laparoscopy. Participants will be allocated 1:1 to active taVNS or sham stimulation using permuted block randomization with concealed allocation. Blinding is maintained for participants, anesthesia providers, surgeons, postoperative ward staff, outcome assessors, and data analysts. Active taVNS will be applied to the left cymba conchae (20 Hz, 250 μs) in two sessions: 30 min before anesthesia induction and 5 min after extubation. The sham stimulation current amplitude will be incrementally increased until the participant perceives a tingling sensation; the current will then be immediately discontinued. Each session will last 30 min with continuous frontal electroencephalography (EEG) monitoring (0.5–45 Hz) at six timepoints. The primary endpoint is the incidence of POSD on postoperative day 1 (AIS score ≥ 6). Secondary endpoints include sleep quality trajectory (AIS, actigraphy), anxiety and depression (HADS), recovery quality (QoR-15), and exploratory EEG spectral analyses.

**Discussion:**

This trial is the first to introduce a perioperative dual-session taVNS protocol integrated with continuous EEG monitoring, investigating its preventive effects on acute POSD in gynecologic laparoscopic patients through a comprehensive set of mechanistic and clinical endpoints. Comprehensive multidimensional assessment combines subjective, objective, and mechanistic (EEG spectral analysis) measures. If proven effective, taVNS could offer a safe and cost-effective non-pharmacological adjunctive therapy for managing POSD in the perioperative setting. Furthermore, the findings have the potential to elucidate how perioperative cortical oscillatory dynamics regulate postoperative sleep quality, offering mechanistic insights for future neuromodulation interventions.

**Clinical trial registration:**

http://www.chictr.org.cn, identifier ChiCTR2600120222.

## Introduction

1

Postoperative sleep disturbance (POSD) is observed in up to 62% of patients undergoing gynecologic laparoscopy, representing a substantial clinical burden (1, 2). This condition typically manifests on the first postoperative night and may persist for several days, significantly contributing to serious complications including chronic pain (3), delirium (4), cardiovascular events (5), and delayed recovery in Enhanced Recovery After Surgery (ERAS) pathways (6). The pathophysiology of POSD may be attributed to a multifactorial etiology, encompassing the disruption of the sleep-wake cycle due to the administration of general anesthetics, in conjunction with inflammation induced by surgical trauma and heightened sympathetic activity (7). These factors collectively contribute to postoperative reductions in rapid eye movement (REM) sleep, slow-wave sleep, and result in sleep fragmentation (5).

Current mainstay treatments rely primarily on pharmacological interventions such as dexmedetomidine (8), melatonin, and zolpidem (9); however, their routine use is limited by adverse effects including respiratory depression, hypotension, bradycardia, and delirium (10). Non-pharmacological interventions such as earplugs, eye masks, relaxation training, music therapy, and aromatherapy have been attempted to improve POSD (11). However, the efficacy of these methods varies considerably, and the quality of available evidence is generally low. In recent years, brain function modulation techniques, as emerging non-invasive neuromodulation approaches, have shown potential in ameliorating POSD. Du et al. found in a randomized, double-blind, sham-controlled trial that a single session of prefrontal transcranial alternating current stimulation significantly reduced the incidence of POSD on the first day after gynecological laparoscopic surgery (12). Nevertheless, this method still has certain limitations, including high equipment cost, complex operation procedures, and possible adverse reactions, which limit its widespread clinical adoption. Consequently, there is a critical demand for therapies that are safe, effective, well-tolerated, and easily implemented to enhance postoperative sleep quality.

Transcutaneous auricular vagus nerve stimulation (taVNS) is a non-invasive neuromodulation approach that delivers electrical pulses to auricular branches of the vagus nerve. By stimulating vagal afferent fibers, taVNS engages brainstem–autonomic pathways (including projections to the locus coeruleus) and modulates thalamo–cortical activity, which may shift cortical arousal dynamics and thereby improve sleep–wake regulation, particularly during perioperative neuroplastic windows. Consistent with this mechanism, prior studies suggest taVNS may reduce POSD (13, 14). Randomized sham-controlled trials demonstrate that taVNS significantly improves sleep quality scores, enhances slow-wave sleep continuity, and boosts daytime functioning in patients with chronic insomnia (15, 16). Prior research indicates that taVNS modulates EEG power spectral density by mitigating reductions in delta power and increases in alpha/beta power associated with negative emotional states (17), with significant effects observed in the prefrontal region (18). Molefi et al. demonstrated that taVNS modulates EEG theta spectral power during visually induced motion sickness, a negative physiological state (19). These findings suggest that taVNS may restore cortical electrophysiological homeostasis, providing a potential neurophysiological basis for sleep improvement. Despite evidence that taVNS modulates EEG patterns and that perioperative EEG characteristics are predictive of POSD, it is unclear whether taVNS delivered can effectively modulate EEG changes to prevent acute sleep disruption.

This protocol describes a single-center randomized, double-blind, sham-controlled trial evaluating whether a dual-session taVNS regimen administered at two perioperative timepoints–30 min before anesthesia induction and 5 min after extubation–reduces the incidence of clinically significant POSD on postoperative day 1 (AIS ≥ 6). Active taVNS will be applied to the left cymba conchae using a predefined stimulation parameter set, while sham stimulation uses an identical device and blinded sensory masking procedures. Continuous frontal EEG will be acquired during the stimulation periods to enable predefined analyses of taVNS-related spectral modulation and to explore EEG biomarkers associated with subsequent sleep outcomes.

## Methods

2

### Study design

2.1

This single-center, prospective, randomized, double-blind, sham-controlled trial will be conducted at Fujian Maternity and Child Health Hospital. A total of 116 participants will be enrolled for elective gynecologic laparoscopic surgery under general anesthesia. The Ethics Committee of Fujian Maternity and Child Health Hospital approved this protocol (approval number 2026KY074), and it is registered with the Chinese Clinical Trial Registry (ChiCTR2600120222). Participants will be thoroughly informed about the study procedures and will provide written consent before enrollment. The protocol is reported in accordance with the SPIRIT 2013 statement. A flowchart illustrating participant flow through recruitment, interventions, and assessments is presented in Figure 1. The schedule of events is presented in Table 1.

**FIGURE 1 F1:**
[figure not shown]
Flowchart of the study design.

**TABLE 1 T1:** Study schedule for data measurements.

Study period											
	Enrollment	Allocation	Post allocation								
Timepoint	Pre1	0 d	T0	T1	T2	T3	T4	T5	POD 1	POD 2	POD 3
Enrollment											
Eligibility screen	X										
Informed consent	X										
Random allocation		X									
Interventions											
Active taVNS				X				X			
Sham taVNS				X				X			
Assessments											
Baseline data	X	X									
EEG			X	X	X	X	X	X			
AIS	X								X	X	X
HUAWEI WATCH GT2	X								X	X	X
QoR-15	X								X		
NRS	X								X		
PSQI	X										
HADS-A	X								X	X	X
HADS-D	X								X	X	X
Adverse events	Record at any time at any time at any time										

Pre1 for preoperative day 1, T0, preoperative baseline (5 min before taVNS); T1, preoperative sustained stimulation period (20–30 min taVNS); T2, post-induction (5 min after intubation); T3, intraoperative maintenance (20 min after incision); T4, peri-extubation (end of surgery); T5, postoperative sustained stimulation (20–30 min post-taVNS). POD 1–POD 3 for postoperative days 1–3; taVNS, transcutaneous auricular vagus nerve stimulation; EEG, electroencephalography; AIS, Athens Insomnia Scale; QoR-15, 15-item Quality of Recovery questionnaire; NRS, numeric rating scale; PSQI, Pittsburgh Sleep Quality Index; HADS-A/HADS-D, Hospital Anxiety and Depression Scale-Anxiety/Depression subscale.

### Participants

2.2

Potential participants will be screened for eligibility during the preoperative assessment, typically scheduled 1 day prior to surgery. Those meeting eligibility criteria will receive detailed written and verbal study information, have the opportunity to ask questions, and provide written informed consent. Participation is voluntary, and individuals may withdraw at any time without impacting their standard clinical care.

#### Inclusion criteria

2.2.1

Participants will be eligible if they are aged 18–65 years, classified as ASA physical status I–II, have a BMI between 18 and 30 kg/m^2^, and be scheduled for elective gynecologic laparoscopic surgery expected to last at least 60 min. Additionally, they must be proficient in Mandarin Chinese with the ability to provide written informed consent.

#### Criteria for exclusion

2.2.2

(1) Broken skin, infection, or inflammation of the external ear or auditory canal; history of tinnitus, Meniere’s disease, or cardiac arrhythmia with symptoms; (2) Presence of an implanted cardiac pacemaker, defibrillator, or other active implantable device; (3) History of neuropsychiatric disorders, such as depression, anxiety, epilepsy, or schizophrenia; (4) Severe hepatic impairment (Child-Pugh class B or C) or renal impairment (eGFR < 60 mL/min/1.73 m^2^ as per the CKD-EPI equation); (5) Planned postoperative ICU admission; (6) Pregnancy or breastfeeding.

#### Dropout criteria

2.2.3

(1) Occurrence of serious adverse events attributed to the intervention or surgical procedure; (2) voluntary withdrawal by the participant; (3) intraoperative conversion to open surgery or unplanned admission to the ICU; and significant deviations from the study protocol affecting primary outcome assessment.

### Randomization and blinding

2.3

An independent statistician will use SPSS (version 26.0, IBM Corp.) to create the allocation sequence through permuted block randomization with randomly varying block sizes of 4 and 6, ensuring balanced allocation throughout the enrollment periods. Participants will be randomly allocated to either active taVNS or sham stimulation in a 1:1 ratio. The statistician will prepare sequentially numbered, sealed, opaque envelopes with group assignments, which will be stored in a locked cabinet accessible solely to a designated unblinded device coordinator. This coordinator responsible exclusively for device preparation will open the envelopes and configure the devices in the pre-anesthesia holding area. Following device connection, the coordinator will exit and have no further contact with participants, clinical care, or outcome assessments.

Throughout the trial, group allocation will remain concealed from anesthesia providers, surgeons, outcome assessors, postoperative ward staff, participants, and data analysts. To ensure participant blinding, identical electrode placement and device appearance will be used for both groups. All devices will display identical interface indicators regardless of stimulation status. Participants will be informed that “both interventions involve ear stimulation with variable mild sensations; individual perception does not indicate assignment.” To maintain assessor blinding, the unblinded device coordinator will ensure that the device interface remains concealed from clinical staff and will not participate in any outcome assessments. Unblinding will be permitted only for serious adverse events that require knowledge of allocation for clinical management. The principal investigator will hold the master randomization key in a sealed, signed envelope. All unblinding events will be recorded along with their reasons and timestamps.

Blinding integrity will be assessed using Bang’s Blinding Index (BI) (20) at two time points: immediately following the second stimulation session and on POD 3. Bang’s Blinding Index for each arm = (correct guesses − incorrect guesses)/(total participants in that arm), ranging from −1 to 1, with 0 indicating perfect blinding. A two-sided 95% confidence interval for BI will be constructed for each arm. If the interval excludes 0 for either arm, indicating statistically significant deviation from random guessing, blinding will be deemed inadequate, and sensitivity analyses will compare primary outcomes with and without potentially unblinded participants.

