
### EEG power spectrum processing

2.5

Frontal quantitative EEG parameters will be obtained using the ConView YY-105 anesthesia depth monitoring system, employing bilateral frontal electrodes at a sampling rate of 500 Hz. EEG power spectral density will be estimated using the multitaper method (15 tapers, time-half bandwidth product = 8) with a 4-s window length and 50% overlap (2-s step), implemented in MATLAB’s pmtm function. The bandpass filter (0.5–45 Hz) will be applied as a zero-phase filter using forward-reverse filtering to avoid phase distortion. Artifact-free epochs will be extracted at six predetermined time points: T0 (pre-stimulation baseline): 5 min prior to the first taVNS session; T1 (preoperative sustained stimulation), 20–30 min following the initiation of taVNS; T2 (post-induction), 5 min after tracheal intubation; T3 (intraoperative maintenance), 20 min subsequent to the skin incision; T4 (peri-extubation), at the conclusion of surgery, immediately preceding emergence from anesthesia; and T5 (postoperative sustained stimulation), 20–30 min after the initiation of postoperative taVNS.

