### Study interventions

2.6

The interventions will be administered at two specific time points: 30 min before the induction of anesthesia and 5 min after tracheal extubation in the PACU, with each session lasting 30 min. Prior to the initiation of stimulation, the left auricle will be cleansed using gauze moistened with a saline solution. The unblinded coordinator will position the taVNS device (model taVNS501, Reshen Medical Technology Co., Ltd., Changzhou, China) according to the randomization assignment.

Participants assigned to the taVNS group will undergo stimulation at the left cymba conchae, an area innervated by the auricular branch of the vagus nerve. This stimulation will be administered using a pulse frequency of 20 Hz and a pulse width of 250 μs. The stimulus amplitude will initially be set to zero and will be gradually increased until the participant experiences a tolerable tingling sensation, typically within 30 s, which will be maintained throughout the 30-min session. In the sham group, the electrode placement will be identical to those of the active taVNS group using the same stimulation parameters. The stimulus amplitude will be incrementally increased until the participant perceives a tingling sensation after which the current will be immediately discontinued. The device will remain powered on, with identical auditory and visual cues, for the entire 30-min session to ensure the absence of sustained neuromodulatory effects while preserving participant blinding.

During each stimulation, participants will remain in a supine position while undergoing continuous monitoring through electrocardiography, pulse oximetry, and noninvasive blood pressure assessment. Trained personnel will provide constant observation of the participants. Stimulation will be immediately stopped if any of the following occur: (1) unbearable discomfort; (2) oxygen saturation (SpO_2_) drops below 90%; (3) heart rate falls below 50 beats per minute or decreases by more than 20% from the initial rate; (4) a new arrhythmia begins; (5) hemodynamic instability, defined as systolic blood pressure below 90 mmHg or above 180 mmHg; or (6) any significant adverse event. The attending physician will decide on the suitable clinical management.

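### EEG recorded while 20 Hz current runs in the active arm only could reveal allocation to people the protocol declares blinded, and the stated safeguards cover only the stimulator

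*Protocol article*

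**What the plan says.** Section 2.3 states that, throughout the trial, "group allocation will remain concealed from anesthesia providers, surgeons, outcome assessors, postoperative ward staff, participants, and data analysts". The means it describes are identical electrode placement and device appearance, identical indicators, and a stimulator interface kept out of clinical staff's sight. The EEG display and the EEG files are not mentioned.

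In section 2.6 the active arm is stimulated "using a pulse frequency of 20 Hz and a pulse width of 250" microseconds. The amplitude is raised to a tolerable tingling, "which will be maintained throughout the 30-min session". In the sham arm it is raised until tingling is felt, "after which the current will be immediately discontinued".

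The Introduction says: "Continuous frontal EEG will be acquired during the stimulation periods". Section 2.5 defines "T1 (preoperative sustained stimulation), 20–30 min following the initiation of taVNS", and T5 in the same way for the postoperative session. The recorder is the ConView YY-105, which section 2.4 also uses to judge anesthetic depth. On artifact, section 2.5 says only this: "Artifact-free epochs will be extracted at six predetermined time points".

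**The concern.** At T1 and T5 the arms differ by a physical signal of known frequency, and the recording covers that frequency. Anyone who sees a 20 Hz line in a trace or spectrum can infer active stimulation. Coded A/B group labels would not prevent this, because the group that carries the line is the active one.

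The decisions most exposed need judgement:

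- which epochs count as free of artifact (section 2.5);
- which deviations are significant enough for dropout (section 2.2.3);
- who is left out of the per-protocol set (section 2.11).

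Section 2.11 also relates 30 EEG variables, T1 and T5 included, to postoperative sleep disturbance, so EEG and primary outcome meet in one analysis. The planned blinding check in section 2.3, Bang's index by arm, is a check on participants. None is described for providers or analysts.

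**Working it through.** The plan gives no figure for this leak. The check therefore asks whether the passages allow it, and how large an artifact would have to be.

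**1. Is current on in one arm only when EEG is taken?** Yes. T1 and T5 lie 20–30 min into a 30-min session (section 2.5). Active current lasts the whole session and sham current stops after titration (section 2.6). The Table 1 footnote for T5 is looser, but section 2.5 counts from the start of postoperative stimulation.

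**2. Does the signal fall in the analysed range?** Inputs from section 2.5: window T = 4 s, time-half-bandwidth product NW = 8, 15 tapers.
- Tapers: 2NW − 1 = 15, as stated.
- Half-bandwidth: W = NW/T = 8/4 = 2 Hz.
- A 20 Hz line spreads over 18–22 Hz, inside beta (12–25 Hz). A 40 Hz line spreads over 38–42 Hz, inside gamma (25–45 Hz).
- Peak frequency within each band is itself an outcome (section 2.7.2), so a strong line would show as a reported value.

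**3. Does choosing artifact-free epochs remove it?** No on/off cycle is stated. With uninterrupted pulsing, each window holds 20 × 4 = 80 pulses, so no active-arm window at T1 or T5 is free of stimulation. Visible artifact then either stays in the spectra or causes rejections mainly in the active arm. Both mark the arm.

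**4. How large must the line be?** Assumptions, none from the protocol: 1/f background, beta power 5 or 20 µV², a 5-min record, and equal lines at 20 and 40 Hz. The measure is power at 20 Hz divided by the mean power at 16.5 and 23.5 Hz. A simulation with the plan's passband and multitaper settings, 15 records per cell, gave (SD in brackets):

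| Line amplitude | Beta 5 µV² | Beta 20 µV² |
|---|---|---|
| none | 0.97 (0.04) | 0.97 (0.03) |
| 0.25 µV | 0.99 (0.03) | 0.95 (0.03) |
| 0.5 µV | 1.08 (0.04) | 0.99 (0.02) |
| 1 µV | 1.34 (0.05) | 1.07 (0.05) |
| 2 µV | 2.47 (0.07) | 1.33 (0.04) |
| 5 µV | 10.33 (0.22) | 3.31 (0.07) |

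Hand check at 2 µV:
- Line power is a²/2 = 2 µV². Spread over 2W = 4 Hz, that is 0.5 µV²/Hz.
- With background c/f and beta power 5, c = 5/ln(25/12) = 6.81. The neighbours average 6.81 × (1/16.5 + 1/23.5)/2 = 0.351.
- The ratio is 0.97 + 0.5/0.351 = 2.39. With beta power 20 the neighbours average 1.405, and the ratio is 0.97 + 0.5/1.405 = 1.33. Both are close to the simulation.

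Three SDs of the no-line ratio are 0.09 to 0.12. A line of 0.25 µV does not stand out, 0.5–1 µV is borderline or visible depending on background, and 2–5 µV is plain. Beta and gamma peak frequency fell in 18–22 and 38–42 Hz in every record from 2 µV (beta 5), or at 5 µV but not at 2 µV (beta 20).

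**5. What pulse at the forehead would that take?** The duty cycle is 20 × 0.00025 = 0.005. A monophasic train gives a 20 Hz line of about 2 × 0.005 = 0.01 of pulse height, so 2 µV needs about 200 µV (0.2 mV). For a symmetric biphasic pulse the factor is multiplied by 2 sin(π × 0.005) = 0.0314, so 2 µV needs about 6.4 mV. The protocol gives neither waveform nor amplitude, so this gap of about 30-fold stays open.

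**The case against.** A reader might infer that the double-blind fails for anesthesia providers and analysts, with all 58 active participants identifiable. The documents do not support that. Artifact size at the forehead is unknown and may be too small to see, so 58 is a ceiling and not an estimate. The SDs above describe an offline average in idealised stationary noise. They say nothing about a live screen, and they ignore frontal muscle activity and differences between patients in the shape of the beta spectrum.

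For anesthesia providers the case is thinner still. The depth target applies during surgery, when no current runs, and the protocol does not say who watches the EEG before induction or in the PACU.

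A reader might also infer bias in the primary result. AIS is a subjective scale with a fixed cutoff, compared by a prespecified chi-square test under intention to treat. Outcome assessors and ward staff are not shown to see EEG. The per-protocol analysis is not the main one, and section 2.11 calls the EEG spectral analyses exploratory.

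Finally, analyst roles, file coding and lock order are commonly left to a full protocol or analysis plan, and an artifact-removal step described there could largely close the analyst route. All this stands as a limit on size. What remains is that the article makes an unqualified blinding claim for named roles, lists its safeguards, and describes a recording that those safeguards do not cover.

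**Conclusion.** The point holds as a credible, unproven route to unblinding that the plan should close. It rests on the protocol's own timing, frequency and passband, and on two assumptions: that pulsing is uninterrupted, and that artifact reaches the frontal electrodes. Over the assumed range the result runs from undetectable (about 0.25 µV or less) to obvious (about 2–5 µV). Whoever processes the EEG is most exposed, and staff near the monitor in the two awake sessions less certainly. The decisions at risk are epoch rejection, the deviation list and the per-protocol set. Any effect on the primary AIS comparison is indirect and cannot be quantified from the document. The sample size is not affected.

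**What to change.** Add to sections 2.3 and 2.5:

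- (a) During the two awake sessions, the EEG waveform and spectrum are recorded but kept out of blinded staff's view. The monitoring that section 2.6 lists for these sessions (electrocardiography, pulse oximetry, blood pressure) stays unchanged.
- (b) EEG files carry separate codes. The primary AIS analysis, deviation list and per-protocol set are locked before blinded analysts open T1/T5 EEG or its rejection counts. Meanwhile, signal quality is checked by someone with no role in outcomes or in those decisions, for example the person who already processes the EEG.
- (c) Epochs are rejected by a fixed automated rule applied alike in both arms.

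The cost is a screen cover or display setting in two 30-min sessions and a fixed order of work, with no extra patients or visits. The downsides are that EEG analysis starts after the primary lock, and that blinded staff cannot check T1/T5 signal quality themselves.

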#### Main outcome

2.7.1

The primary endpoint is the incidence of POSD on POD 1, defined as an Athens Insomnia Scale (AIS) score ≥ 6. The AIS is a validated eight-item instrument measuring nocturnal sleep parameters and daytime functioning, with total scores ranging from 0 to 24 (22).

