### Data collection and management

2.9

Outcome and safety variables will be systematically collected across three distinct phases: preoperative, intraoperative, and postoperative. During the preoperative phase, demographic data, medical history, surgical information, laboratory values, and baseline assessments, including AIS, HADS, NRS for pain, and QoR-15, will be recorded at the enrolment visit immediately preceding the initial taVNS session. In the intraoperative phase, data on the duration of anesthesia and surgery, tracheal intubation time, estimated blood loss, fluid infusion volume, medication administration, and continuous EEG parameters will be meticulously documented. Postoperatively, the AIS and HADS will be assessed in the evenings of POD 1, 2, and 3. Additionally, the QoR-15 and NRS pain scores, both at rest and during movement, will be evaluated on the morning of POD 1, alongside the documentation of clinical outcomes and any adverse events.

All data will be systematically recorded using standardized case report forms (CRFs) and subsequently double-entered into an encrypted electronic database by two independent research assistants. A random sample comprising 10% of the CRFs, stratified according to the enrolment sequence, will undergo verification against the original medical records. The data manager will be responsible for generating queries related to missing or inconsistent values, with the principal investigator overseeing their resolution. In compliance with institutional policy and ICH-GCP guidelines, original CRFs will be securely stored in a locked cabinet with restricted access for a minimum duration of 5 years. The electronic data will be hosted on hospital servers, safeguarded by SSL encryption, automated backups, and role-based access control, ensuring access is limited to authorized study personnel.

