### Sample size calculation

2.10

The primary outcome is the incidence of POSD on POD 1, defined as an AIS score ≥ 6. Based on our internal pilot study (*N* = 20; taVNS *n* = 10, sham *n* = 10), the incidence of POSD (AIS ≥ 6) was 20% in the taVNS group compared to 45% in the sham group. Sample size was calculated using PASS 15.0 (NCSS, LLC) for a two-sided chi-square test comparing two independent proportions, with the following parameters: P1 (sham) = 0.45, P2 (taVNS) = 0.20, α = 0.05 (two-sided), power = 0.80. This calculation indicated a need for 52 evaluable participants per group. Accounting for an anticipated 10% dropout rate based on comparable perioperative neuromodulation trials, the final target enrollment is 116 participants (58 per group).

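### The blinding check allows guesses made on POD 3, after the POD 1 sleep outcome, to decide who leaves a sensitivity analysis, and it treats a well-fooled sham arm as failed blinding

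*Protocol article*

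**What the plan says.** Section 2.3 (Randomization and blinding) sets three rules.

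- **Timing.** Guesses are collected "immediately following the second stimulation session and on POD 3".
- **Trigger.** The index is defined as "Bang’s Blinding Index for each arm = (correct guesses − incorrect guesses)/(total participants in that arm"), with a two-sided 95% interval for each arm. "If the interval excludes 0 for either arm, indicating statistically significant deviation from random guessing, blinding will be deemed inadequate". No direction is given, and neither time point is named as the deciding one.
- **Consequence.** "sensitivity analyses will compare primary outcomes with and without potentially unblinded participants". The article does not say what makes a participant potentially unblinded.

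Section 2.7.1 fixes the outcome: "The primary endpoint is the incidence of POSD on POD 1, defined as an Athens Insomnia Scale (AIS) score ≥ 6". Section 2.9 says that "the AIS and HADS will be assessed in the evenings of POD 1, 2, and 3". By the POD 3 guess, each participant has therefore lived through and reported the primary outcome. Section 2.11 makes intention-to-treat the main analysis.

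**The concern.** A guess made after the outcome can be caused by the outcome. A patient who slept well may conclude that the stimulation was real, and one who slept badly that it was sham. Excluding correct guessers would then take good sleepers out of the active arm and poor sleepers out of the sham arm. The comparison among those who remain is pushed against the treatment even if nobody detected their allocation.

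This matters because the endpoint is self-reported and the two arms feel different: section 2.6 sustains the tingling in the active arm and stops the current in the sham arm. A reader who doubts the blinding will look for an answer, and this is the only analysis the article offers.

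The trigger has its own fault. A sham index below 0 means that more sham patients guessed wrongly than rightly. That is what a convincing sham produces, yet the rule calls it inadequate blinding.

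**Working it through.** **Inputs from section 2.10.** "P1 (sham) = 0.45, P2 (taVNS) = 0.20, α = 0.05 (two-sided), power = 0.80". "This calculation indicated a need for 52 evaluable participants per group". Enrolment is 58 per group.

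**The plan's own figure.** With unpooled variance, n = (1.96 + 0.8416)² × (0.45×0.55 + 0.20×0.80) / 0.25² = 7.849 × 0.4075 / 0.0625 = 51.2, so 52 per group. Then 52 / 0.90 = 57.8, so 58. The planning rates are used below as stated.

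**Assumptions not in the article.** Potentially unblinded means a correct guess. There are no 'don't know' answers. Guesses depend only on sleep: a patient without POSD guesses active with probability g, and a patient with POSD guesses sham with probability g.

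**POSD among those kept (incorrect guessers).**

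- Active arm: 0.20g / [0.20g + 0.80(1−g)]
- Sham arm: 0.45(1−g) / [0.45(1−g) + 0.55g]

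At g = 0.70 the active arm gives 0.14 / (0.14 + 0.24) = 36.8%, and the sham arm 0.135 / (0.135 + 0.385) = 26.0%.

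| g | Active | Sham | Apparent risk reduction | Expected BI, active / sham | Rule fires |
|---|---|---|---|---|---|
| 0.50 | 20.0% | 45.0% | 25.0 points | 0.00 / 0.00 | 9% |
| 0.60 | 27.3% | 35.3% | 8.0 points | 0.12 / −0.02 | 19% |
| 0.65 | 31.7% | 30.6% | −1.1 points | 0.18 / −0.03 | 31% |
| 0.70 | 36.8% | 26.0% | −10.9 points | 0.24 / −0.04 | 48% |

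**Break-even.** The two kept odds are equal when [g/(1−g)]² = (0.45/0.55) / (0.20/0.80) = 3.27. So g/(1−g) = 1.81 and g = 0.644.

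**How often the rule fires.** The last column is an exact binomial calculation with 58 per arm, one time point, and the interval BI ± 1.96 √[(1−BI²)/58]. On the positive side an arm triggers at 37 or more correct guesses of 58, that is (37 − 21)/58 = 0.28. Evaluating both time points would raise these figures.

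**Contrast: guesses unrelated to sleep.** If 60% to 80% of each arm guesses correctly for reasons unrelated to sleep, the simulated risk reduction among those kept stays at 24.9 to 25.1 points (20,000 runs, 52 per arm). The bias comes from the link between outcome and guess, which a guess taken before the POD 1 outcome cannot owe to that outcome.

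**The trigger's direction.** Suppose 65% of 58 sham patients believe they were stimulated. BI = 0.35 − 0.65 = −0.30, the half-width is 1.96 √[(1 − 0.09)/58] = 0.25, and the interval is about −0.55 to −0.05. It excludes 0, so the rule declares blinding inadequate. This needs no assumption about sleep.

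**The case against.** The strongest reply is that the harmful rule is partly inferred. Section 2.3 does not say that correct guessers are dropped, nor that the POD 3 guess decides. The same section also records actual unblinding events, which could be what the term refers to, and the exact definition might sit in a fuller document. This stands as a limit. However, the term follows directly on a rule built from correct and incorrect guesses, so correct guessing is the natural reading, and the article lists POD 3 as one of the two assessments on which that rule operates.

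A reader might infer that the trial's result will be reversed. The documents do not support that. The reversal needs the POD 3 guess, the correct-guess reading and a fairly strong link between sleep and guess, all together. No guess data are given, and the differing sensations in section 2.6 offer a cue that does not depend on the outcome. Even at g = 0.70 the analysis would not run in about half of trials. The comparison is reported with and without the participants in question, and the main analysis keeps everyone.

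A reader might also infer that requiring the lower limit of BI to exceed 0 would cure the trigger. It would not: if most patients in both arms believe they were stimulated, the active index is above 0 and the rule still fires through that arm.

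Finally, an analysis by early guess still conditions on something measured after randomisation. That is true, and is why it should be descriptive only.

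**Conclusion.** The point holds for a triggered sensitivity analysis, not for the primary result. The text permits a guess made after the outcome to decide whether blinding failed and who is left out. If that guess follows sleep, the exclusion is biased against the treatment, and a link of about 64% is enough to erase the planned effect. These sizes rest on the planned rates, the correct-guess reading, no 'don't know' answers, and guesses driven by sleep alone. The strength of the link is unknown, so the range is the result and no single row of the table is a forecast.

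The fault in the trigger is independent of those sleep assumptions: as stated, the rule labels a sham arm that mostly guessed wrongly as inadequately blinded.

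**What to change.** Amend section 2.3 before any guesses are seen:

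1. Base the blinding assessment, and any sensitivity analysis that uses guesses, only on the guess taken right after the second session. Report the POD 3 index descriptively.
2. Do not treat a sham index below 0 as unblinding by itself. Interpret the two arms' indices together, so that a pattern in which most patients in both arms guess active is reported as a shared belief in treatment.
3. Replace the exclusion with a descriptive analysis that keeps all randomised participants and shows the treatment effect by early guess. State that the early guess is itself a post-randomisation variable that sensation may influence.

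The cost is a few sentences. Both guesses are already collected, and neither the sample size nor the primary analysis changes.
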